### Medications/treatments permitted during the trial

Psychotropic medications with serotonergic activity will not be permitted during the study. Smoked cannabis can also enhance the effects of narcotic medications such as codeine, morphine and oxycontin. However, we will use a high CBD formulation that is suggested to be minimal risk and is not expected to adversely interact with these medications [54]. Therefore, if participants are taking these medications on a regular basis they will be allowed enrolment in this study but will be monitored by the Qualified Investigator and Principle Investigator of these studies.

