CBD appears to work via a number of receptors, including non-cannabinoid receptors, such as the G-protein-coupled receptors serotonin 1A and adenosine A2a, the ligand-gated vanilloid receptor ion channels, and the nuclear peroxisome proliferator-activated receptors [4, 24]. Collectively, modulation of these receptors can result in extensive anti-oxidative and anti-inflammatory effects, along with influencing hemodynamic activity [4, 25, 26]. Consequently, CBD has the potential to limit blood brain barrier permeability, improve cerebral functional connectivity, and the heart-brain axis interactions following mTBI [4, 24]. To date, no research has examined CBD-mediated neuroprotection in elite contact sport athletes, but such effects have been inferred [3, 4, 27]. Furthermore, specific dosage, pharmacokinetic, and pharmacodynamic data are lacking, or are difficult to compare between studies that use different sources of CBD [28].

This protocol presents the first of a three-part research project aimed at investigating the pharmacological, physiological, and psychological effects of CBD in healthy, young (18–35 years) males. Female participants are excluded as the study needs to be directly applicable to the National Football League (NFL) players due to the funding requirements, requiring our sample to be male. We also predominantly recruited participants that played American style Football. However, our future research will include a similar study in female participants participating in contact sports. The primary objectives and endpoints are to develop an optimal CBD dose based on the pharmacokinetic data in contact-sport athletes. The secondary objectives include direct neurophysiological and pharmacological analyses to understand the mechanism(s) associated with the primary objective findings. The primary research hypothesis is that CBD formulations are non-intoxicating (non-psychotropic), safe, well-tolerated and do not cause adverse physiological or psychological dysfunction. Specifically, a placebo-washout, dose escalation Phase I clinical trial will be conducted to document the effects of increasing dosages of CBD on pharmacokinetic and pharmacodynamic parameters to determine what is an ‘optimal’ formulation for daily administration for physiological function. This dose will be applied to future research studies to understand the influence of CBD on neuroprotection from concussion. The secondary hypotheses are:

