## Methods and design

### Study design

We will complete a two-centre, phase 1, open-label dose escalation study to determine the safety and tolerability of CBD in healthy male athletes. The study will be conducted in two centres in Canada (Regina and Saskatoon, SK). The study consists of a baseline phase, a treatment phase, and a post-dosing phase. Figure 1 illustrates the study visits.

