### Study population

We will recruit 40 participants across two study sites. Eligibility to participate in the study include the following criteria:Healthy male adults between 18–35 years of age that compete (in any level, including recreational, collegiate, professional) in contact sport athletics (including American football, soccer, rugby, wrestling, and hockey).Non-smokers without known medical complications.Ability to maintain commitment to all proposed biopsychological and health questionnaires, and neuro-physiological and physiological laboratory tests.

Participants meeting any of the following criteria are excluded from the study:

Currently under treatment (e.g., by a physician or clinical psychologist) for anxiety, depression, post-traumatic stress disorder, mood disorder, psychotic disorders or any cerebrovascular and cardiovascular complications.Unable to maintain commitment to all proposed biopsychological and health questionnaires, and neuro-physiological and physiological laboratory tests.

Since the study is employing a continuous dose escalation design, a placebo-washout design will be implemented. All participants will first intake a placebo for 2 weeks prior to beginning their CBD dosing protocol. As such, no participant randomization of participants will occur, and neither the study participants nor the study investigators will be blinded to the CBD dose. As we will likely recruit the majority of the participants from the university population, they are expected to be in their off-season.

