### Procedures

#### Baseline Phase

##### Visit 1 (Day -15): Consent

Participants who meet the eligibility criteria and have signed the informed consent will be enrolled into the study. From each participant, a medical history (including demographics such as height, body mass), health questionnaires (paper and pen), and a saliva sample will be taken. Participants will receive a logbook to record any side effects associated with the study product during the treatment phase. This session will take approximately 20–30 min to complete. The body mass recorded at this initial visit will be used for the dosing regimen.

Participants will be asked to refrain from taking Cannabis or Hemp products between study Visit 1 and 2 (approximately 2 weeks later) to ensure undetectable cannabinoid levels in their blood at the commencement of the treatment phase. As well, participants will be instructed to not smoke, use chewing tobacco, or use any Cannabis or Hemp products besides the study CBD for the duration of study. These are important requirements to continue in this study. Participants will be asked to not complete Visit 1 and to terminate the study if they feel that they cannot adhere to these requirements.

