### Withdrawal criteria

Study participants may withdraw from the study at any point. Participants will be withdrawn if they suffer from any intolerable adverse effects resulting from the CBD intervention, if they fail to attend required site visits, or they are noncompliant with the CBD dosing regimen. For transparency, though, all participants withdrawn from the study will be included in the final report.

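### Regular narcotic users may enrol in a safety study of healthy men, adding an avoidable rival cause for sedation and nausea events in any such man

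*Protocol article*

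**What the plan says.** All references are to the protocol article.

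- **Purpose.** Study design describes an "open-label dose escalation study to determine the safety and tolerability of CBD in healthy male athletes". Background adds: "The primary research hypothesis is that CBD formulations are non-intoxicating (non-psychotropic), safe, well-tolerated".
- **Who may enter.** Study population asks for healthy men aged 18 to 35 in contact sport, and for "Non-smokers without known medical complications". The treatment-related exclusion begins "Currently under treatment (e.g., by a physician or clinical psychologist) for anxiety, depression, post-traumatic stress disorder" and goes on to mood and psychotic disorders and to cerebrovascular and cardiovascular complications. It names neither pain nor narcotic use.
- **What they may take.** Medications/treatments permitted during the trial bars serotonergic psychotropics. It then notes that smoked cannabis can strengthen the effect of narcotics (codeine, morphine and oxycontin are the examples), says no adverse interaction is expected with a high-CBD product, and concludes: "if participants are taking these medications on a regular basis they will be allowed enrolment in this study". The safeguard follows directly: "but will be monitored by the Qualified Investigator and Principle Investigator of these studies".
- **What is rated.** Safety parameters lists sleepiness/lethargy, irritability, nausea/vomiting and diarrhoea on the adverse-event scale.
- **When a man is taken off.** Withdrawal criteria: "Participants will be withdrawn if they suffer from any intolerable adverse effects resulting from the CBD intervention".

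**The concern.** A man who takes a narcotic regularly usually has a condition for which it was prescribed. Admitting him sits awkwardly with a cohort described as healthy and free of known medical complications. The article does not say how the two rules combine, so the two centres could screen the same candidate differently.

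Sedation and nausea are familiar narcotic effects, and they are also items on this trial's adverse-event scale. The stated aim is to learn whether CBD is safe and well tolerated up to 30 mg/kg/day. In a man taking both, an event at a higher dose level has more than one plausible cause. At stake are the reading of such events in individual men and the decision to withdraw a man because of CBD.

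**Working it through.** The plan gives no figure on this point, so there is none to reproduce. The check has two parts: the text, and an illustration of scale.

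**1. Do the rules conflict?** Visit 1 enrols men who meet the eligibility criteria. The permission says that regular narcotic use does not bar entry. Both can apply together: a man whose underlying condition counts as a medical complication fails, and one who passes may keep his drug. Medical complications are not defined. The tension is therefore inferred from what regular narcotic use normally implies.

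**2. What can be separated within one man?** Visit 2 (Day 0) and Visit 3 (Day 15, after the placebo period) both precede CBD. From Day 15 to Day 97 the dose rises by 5 mg/kg/day every two weeks, in every man, openly and in the same order.

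- *Stable narcotic effect:* present before CBD as well, so largely absorbed by the man's own pre-CBD observations.
- *CBD-narcotic interaction that grows with CBD dose:* follows the same course as a CBD dose effect, so not separable in that man.
- *Narcotic dose change during Days 15–97:* confounded with CBD dose, because dose and time move together. This is not far-fetched: Background lists the use of cannabinoids to reduce opioids for chronic pain as an open question.

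**3. How many such men?** Not stated. For an assumed share p of regular users among 40 recruits, the expected number is 40p and the chance of none is (1 − p)^40:

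| Assumed p | Expected users | Chance of none |
|---|---|---|
| 1% | 0.4 | 67% |
| 2% | 0.8 | 45% |
| 5% | 2.0 | 13% |

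**4. How far could a crude event rate move?** With k users, crude rate = [k × user rate + (40 − k) × other rate] / 40. All rates and counts are assumed.

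- User rate 50%, other rate 10%: k = 1 gives (0.5 + 3.9)/40 = 11.0%; k = 2 gives (1.0 + 3.8)/40 = 12.0%; k = 4 gives (2.0 + 3.6)/40 = 14.0%. Without users it is 10.0%.
- User rate 30%, other rate 10%: 10.5%, 11.0% and 12.0%.
- The shift is k × (user rate − other rate)/40. Over other rates of 5–20% and user rates of 30–50%, k = 4 gives 4 × 0.10/40 = 1.0 point to 4 × 0.45/40 = 4.5 points; k = 1 gives 0.25 to 1.1 points. With k = 0 it is nil.

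These shifts include any stable narcotic effect, which the pre-CBD visits largely absorb. They may therefore overstate the bias in a comparison between dose levels.

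**The case against.** The strongest reply is that this is a reasoned choice. The section raises the interaction, says why none is expected, cites a source that is not at hand, and assigns monitoring to both investigators. The choice also suits the programme: Background names opioid use in chronic pain as a gap and asks for applicability to professional football players, and pain is among the outcomes measured. The bans on other products do not show inconsistency. The one in the Visit 1 section, "participants will be instructed to not smoke, use chewing tobacco, or use any Cannabis or Hemp products besides the study CBD", stands beside a stated aim of undetectable cannabinoid levels before treatment, which does not extend to narcotics.

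Most of this stands, and so do the existing safeguards. Medication is recorded on the intake form, calls are made weekly, adverse events are sought at every contact and recorded whatever their cause, and withdrawn men are included in the final report. An interaction is also a genuine tolerability signal in the man concerned, though it would not carry over to men who take no narcotic. The Discussion already discloses the lack of randomisation and blinding.

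A reader might go further and infer that the permission flatly contradicts the eligibility criteria. It does not, because the two rules can be applied cumulatively. Nor is the lack of a stable-dose condition, or of a separate summary for these men, a fault here: a condensed article leaves such detail to the full protocol or analysis plan.

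The reply does not remove the attribution problem in an individual user. The expectation of no interaction is itself untested in this setting: the Discussion says that no study has yet suggested a safe and tolerable daily CBD regimen for contact-sport athletes.

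**Conclusion.** The point holds as a minor design weakness. The permission is explicit and fits poorly with the intended healthy cohort. In any man it admits, a dose-related interaction or a narcotic dose change would be indistinguishable from a CBD dose effect on sleepiness/lethargy or nausea/vomiting, and a withdrawal attributed to CBD would be harder to justify.

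The size is small and rests wholly on assumed numbers of users and assumed event rates. With no users there is no effect. Four users among 40 would move a crude rate by 1.0 to 4.5 points, and since users can be identified at intake, reporting without them removes that shift. What lasts is the reading of individual cases.

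A reader might infer that the trial's safety conclusions or its primary outcome are compromised. The documents do not support that. The Discussion names pharmacokinetic data as the primary outcome, and nothing shows that narcotic use alters it. No material effect on group results is shown either.

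**What to change.** Add regular narcotic use to the exclusion criteria in Study population, and delete the permission in Medications/treatments permitted during the trial. That settles how the two sections relate and removes an avoidable safety risk along with the rival cause.

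The cost is a short amendment, the loss of a few candidates (assumed 0 to 4) who can be replaced so that 40 are still recruited, and slightly narrower applicability to the professional players named in Background. Even if four men were lost and not replaced, the standard error of a 10% event rate would rise only from √(0.09/40) = 4.7 to √(0.09/36) = 5.0 percentage points. The exact one-sided 95% upper bound after zero events would rise from 1 − 0.05^(1/40) = 7.2% to 1 − 0.05^(1/36) = 8.0%.

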### Monitoring of subject compliance

The graduate student researchers who will make weekly phone calls and monitor and encourage logbook completion will monitor participant compliance. Participants will be asked to return all unused study medication in the provided container at each visit as a measure of drug accountability and participant compliance. All unused study medication will be recorded.

### Safety parameters

Participant safety will be assessed using the following parameters:Quality of life questionnaire at Visits 1 and appropriate follow-up visits (Fig. 1).Laboratory testing conducted at Visit 2 and follow-up visits (Fig. 1)Adverse Events monitored and recorded at Visits 2 all subsequent visits. The rating scale includes items related to sleepiness/lethargy, irritability, nausea/vomiting and diarrhea.

### Adverse events

According to the International Council for Harmonisation of Technical Requirements for Pharmaceuticals for Human Use (ICH) guidelines for Good Clinical Practice, an adverse event is any untoward medical occurrence in a participant or clinical investigation participant when administered a pharmaceutical product that does not necessarily have a causal relationship with this treatment. An adverse event can therefore be any unfavorable and unintended sign (including an abnormal laboratory finding), symptom, or illness temporally associated with the use of a medicinal (investigational) product, whether or not related to the medicinal (investigational) product.

### Serious adverse events (Immediately Reportable to the Sponsor)

A serious adverse event is any adverse event that meets any of the following criteria:Fatal (i.e., the adverse event actually causes or leads to death);Life threatening (i.e., the adverse event, in the view of the investigator, places the participant at immediate risk of death). This does not include any adverse event that had it occurred in a more severe form, or was allowed to continue, might have caused death;Requires or prolongs inpatient hospitalization;Results in persistent or significant disability/incapacity (i.e., the adverse event results in substantial disruption of the participant’s ability to conduct normal life functions);Congenital anomaly/birth defect in a neonate/infant born to fathers exposed to study medication;Significant medical event in the investigator's judgment (e.g., may jeopardize the participant or may require medical/surgical intervention to prevent one of the outcomes listed above).

Study Investigators will seek information on adverse events at each participant contact. All adverse events, whether reported by the participant or noted by study personnel, will be recorded. During and following a person's participation in a trial, the investigator/institution should ensure that adequate medical care is provided to them for any adverse events, including clinically significant laboratory values, related to the trial. The investigator/institution should inform a participant when medical care is needed for current illness(es) of which the investigator becomes aware. The study investigators will be responsible for ensuring that all adverse events are recorded and reported to the Sponsor in accordance with the adverse event reporting instructions. Specifically, if the PI and QI agree that the staff-identified adverse event is serious, this will be reported to Health Canada by the Sponsor as per Health Canada regulations, and to the Research Ethics Boards by Site Investigators. Should the serious adverse event be unexpected (SUSAR) and related to the CBD, a report will be sent to Health Canada and the Research Ethics Boards within 15 days. Based on this report, if amendments are required to the informed consent form, this process will be completed and all current participants will be notified of this potential adverse event and be required to re-consent and complete the informed consent process again.

### Direct access to source data/documents

The Investigator acknowledges that some authorities have a duty to monitor the study records to make sure all the information is correct. The study records may be inspected under the authority of the investigator or his qualified designate by representatives of the Sponsor, Health Canada or the Research Ethics Board, as necessary.

### Ethics and dissemination

All information collected on the data collection form will be de-identified and no direct personal identifiers will be recorded. All measures will be taken to maintain confidentiality on collected data. A list connecting the participant’s name to the participant serial number listed on the data collection form will be stored on a password-protected computer and access to this list will be limited to research staff directly involved in the project. As per the Health Canada requirements, data will be stored for 15 years, and the Sponsor shall maintain all records related to the study for a period of 15 years. All data will be de-identified and only aggregated data will be presented at conferences and published in peer-reviewed journals. The data will be stored locally with the investigators.

### Compensation

Participants will each be compensated $250 for completing the entire study. If participants elect to withdraw from the study, they will be paid in proportion to the amount of time that volunteered to participate.

## Human ethics and consent to participate declarations

Ethics approval has been attained for this study from the University of Saskatchewan Research Ethics Board (REB Bio#3455). Health Canada approval (No Objection Letter) was obtained for this clinical trial study, and this study is registered with ClinicalTrials.gov (ID NCT06204003). All participants enrolled in the study are required to provide a signed informed consent document.

## Discussion

This is the first investigation of pharmacokinetics using a dose escalation trial with CBD in an athletic human population. There is limited data available on the dose escalation of CBD that examines the pharmacokinetics, physiological, and psychological profile. Furthermore, the majority of the literature reports on varying routes of administration, and pharmacokinetic research suggests that the half-life, absolute bioavailability, maximum serum concentration reached, and time to achieve maximum serum concentration vary depending on the dose [55].

The study product is given on a mg of CBD per kg body mass basis. Body mass can vary during the course of the study, but to allow for consistency and ability to supply individual dosing units to the participants, mg/kg doses will be based on the participant’s body mass determined during the Baseline Phase. The dose escalation proposed is based on the fact that, to date, there are no studies to suggest an appropriate dosing regimen for CBD products that is safe and tolerable for daily administration in contact sport athletes. Our proposed dosage escalation study, at six different dosages will be taken by all participants to allow us to assess the safety, efficacy and tolerability of the CBD at increasing concentrations. Literature review shows a wide range of CBD oral doses from 100 mg/day to 4500 mg/day have been administered safely [56–58]. Human studies using an acute single dosage of 6000 mg have not produced any serious or severe harmful effects [59]. The dose escalation and optimal dose has not been assessed to date. Consistent with the literature, a 2-week washout phase is used to ensure that no CBD remains in the body from any previous exposure prior to beginning the trial [60]. This will therefore be the first dose escalation CBD study that includes assessment of the optimal dose as assessed by pharmacokinetic activity.

Most studies also utilize arbitrary dosages (i.e., “shotgun approach”) or assess single dose parameters. Therefore, there is a need to understand the influences of varying doses of CBD on the physiological and pharmacological profiles, including the impact of dose escalation, when administered chronically (i.e., months). Ascending doses from 1500 to 6000 mg found that the maximum CBD concentration and half-life all vary depending on dose and the delivery of dose per day (such as twice daily as compared to a single-dose), with further evidence suggesting that the intake of a high-fat diet can increase the bioavailability of CBD by up to five-fold [59]. Therefore, given how different parameters associated with CBD dose and methods of administration all seem to influence its uptake, our first study will aim to address these concerns and provide guidelines for future research to base their designs.

Specific to sport-related concussion, the theoretical framework for the use of CBD as treatment to improved blood flow, cardiac parameters, and to provide neuroprotective benefits by enhancing the integrity of the blood brain barrier has been described [4]. Preliminary evidence was provided with a case series of 4 women with PPCS who showed improvements in cardiovascular parameters and concussion-related symptoms when administered CBD ranging from 50 to 400 mg daily, or a combined 20 mg CBD: 1 mg THC [39]. However, the evidence from a human clinical trial is still lacking. As such, our study will also assess how these physiological parameters are impacted in healthy male contact sport athletes (generally altered during concussion) and suggest an optimal dose for healthy participants to be implemented into a sports season in our future research.

While the study presents with fundamental strengths for assessing changes in physiological, neurophysiological and pharmacological activity, there are limitations associated with our methods. First, the study is not randomized, meaning there is potential for bias in our physiological results in association with higher CBD dosages. Furthermore, participants and researchers are not blinded to the condition, which can bias some of the outcomes. However, our primary outcome is the PK data, which will not be influenced by participant blinding. We are limited to assessing static and dynamic cerebral autoregulation. As such, we will not have an understanding of how cerebrovascular reactivity and neurovascular coupling are affected by CBD. While our participants are required to be at least 18 years of age, little is known about neurodevelopmental process from chronic CBD administration [61]. Regarding pharmacokinetic activity, we are hypothesizing that 2-weeks is sufficient to reach a steady state of CBD plasma concentrations, although research is currently lacking. Finally, given the large amount of time required per participant, we are unable to assess other aspects of cognitive and physical function, such as perceptual-cognitive and functional motor control assessments.

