##### Treatment Phase

Visit 3–9 (Days 15—97).

At Visit 3 (Day 15) participants undergo the same laboratory testing procedures as conducted during the baseline assessments. They will be told to discontinue the Placebo product and will receive the CBD from a study researcher. The CBD product will be supplied as appropriately labelled, individual dosing units (glass vials) and participants will be provided with a hand-out that explains the administration of the CBD product. The first CBD dose at that particular dosing level will be administered to the participant. Participants will be instructed to take an individual dosing unit twice per day, once in the morning at breakfast and once in the evening approximately 10 – 12 h since the morning dose. The study drug will be taken with 250 mL of water and a Blender Bites smoothie ‘puck’ (https://blenderbites.com/). Further, the participants will be asked to record any adverse effects into the Logbook provided to them on Visit 1.

After 2 weeks of treatment, participants will return to the study laboratory for follow-up testing that includes blood and saliva sampling, biopsychological and health questionnaires, and neuro-physiological and physiological laboratory tests. They will return all empty and unused individual dosing units to allow the study research personnel to determine compliance. They will be told to discontinue the current CBD dosing level and will receive a supply of higher dose CBD product according to the dose escalation schedule. Blood samples will be taken prior to the next CBD dose level administration to allow determination of plasma concentrations of CBD and its metabolites prior to increasing the dose. Immediately following the blood sampling, the participant will be administered the new CBD dose level. Participants will be asked to update the researchers regarding any symptoms or adverse events, and to record these in their Logbook. Visit 9 represents the end of the treatment phase. Participants will discontinue the CBD product and will return all empty and unused samples to the study researchers.

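### The PK argument for accepting open labelling does not cover the primary hypothesis of safety, tolerability and no psychological dysfunction

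*Protocol article*

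**What the plan says.** The protocol article makes two different things primary.

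- Background, objective and endpoint: "The primary objectives and endpoints are to develop an optimal CBD dose based on the pharmacokinetic data in contact-sport athletes".
- Background, hypothesis: "The primary research hypothesis is that CBD formulations are non-intoxicating (non-psychotropic), safe, well-tolerated and do not cause adverse physiological or psychological dysfunction".
- Study design, purpose: "open-label dose escalation study to determine the safety and tolerability of CBD in healthy male athletes".

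On blinding, the Study population section says that "neither the study participants nor the study investigators will be blinded to the CBD dose". Everyone takes placebo for two weeks first, and at Visit 3 the switch is announced: "They will be told to discontinue the Placebo product and will receive the CBD from a study researcher". Six dose levels then follow in the same ascending order for all participants.

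The limitations paragraph of the Discussion admits that open conditions may bias part of the results. Its only answer is that "our primary outcome is the PK data, which will not be influenced by participant blinding".

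The logbook handed out at Visit 1 is described as a place to "record any side effects associated with the study product during the treatment phase". The Visit 2 and Treatment Phase sections ask for all adverse effects, with no restriction on cause.

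**The concern.** The defence answers a question about plasma concentrations. The primary hypothesis asks whether participants feel or function worse on CBD, and most of the evidence for that comes from participants' own reports or from staff observation. Both groups know which product and which level is being taken.

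Knowledge of dose rises in step with the dose itself, so any effect of expectation or of unmasked scoring takes the shape of a dose-response. It can run either way. A participant who expects side effects at a high level may report more of them. A participant or observer who expects a calming, well-tolerated product may report or score fewer. Since the hypothesis is absence of harm, the second direction matters at least as much as the first.

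The Discussion part of the Abstract also names psychological and physiological properties among the bases of the optimal dose. It does not say how they are weighed, but bias in them could reach the dose carried into later studies.

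**Working it through.** **Step 1. Which outcomes does the PK argument protect?** The measures sort by exposure as follows.

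- *Little exposed:* plasma CBD and metabolites (Pharmacokinetic assessment), and haematology and chemistry (Physiological and psychological testing). The argument holds here.
- *Less exposed to scoring:* blood pressure and heart rate variability, which are recorded by instrument (Cerebrovascular and cardiovascular protocol).
- *Self-report:* the logbook; the adverse-event rating scale covering sleepiness, irritability, nausea and diarrhoea (Safety parameters); GAD-7, quality-of-life, pain and SCAT6 symptom questionnaires (Health questionnaires); the Leeds sleep questionnaire (Sleep quality assessment). The argument does not reach these.
- *Observed, or possibly needing reader judgement:* non-verbal pain behaviour, the cortical silent period, SICI amplitudes and seismocardiogram intervals. The argument does not reach these either.

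Most of what bears on the words tolerated, non-intoxicating and psychological dysfunction in the hypothesis falls in the last two groups.

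**Step 2. Is there a figure in the plan to reproduce?** No. The documents give no size for expectation or scoring bias.

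**Step 3. How small a bias would matter?** This is an illustration on assumptions, not an estimate. Two inputs are borrowed from Sample size justification and statistics: N = 36 and correlation rho = 0.5, which are stated there for blood pressure and heart rate variability. The rest is assumed: a subjective score with SD 1, no drug effect, equal correlation between periods, and a mean shift rising evenly from 0 on placebo to b SD at the sixth dose (seven periods).

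The seven means are b × k/6 for k = 0 to 6. Their sum of squares about the mean is b² × 28/36 = 0.778 b². For a one-degree-of-freedom linear trend:

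lambda = N × 0.778 b² / (1 − rho) = 36 × 0.778 b² / 0.5 = 56 b², with df = 1 and 35 × 6 = 210.

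| b (SD at top dose) | lambda | chance of p ≤ 0.05, linear trend | omnibus test (6 df) |
|---|---|---|---|
| 0 | 0 | 5% | 5% |
| 0.1 | 0.56 | 11.6% | 7.2% |
| 0.2 | 2.24 | 31.9% | 15.6% |
| 0.3 | 5.04 | 60.8% | 32.9% |
| 0.5 | 14.0 | 96.1% | 79.9% |

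The same algebra works in reverse. If CBD truly worsened a score by b and bias moved it by −b, the means would be flat and the chance of seeing the trend would fall to 5%.

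**Step 4. Logbook wording.** The Visit 1 text ties entries to the product and to the treatment phase, whereas placebo is dispensed at Visit 2, under the Baseline Phase. The instructions at Visit 2 (placebo) and in the Treatment Phase (CBD) use one common sentence without that tie. The Adverse events section counts events whatever their cause. Visit 1 is therefore the odd one out.

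**The case against.** The strongest reply is that this is a declared open-label phase 1 escalation with a PK-based endpoint, and that the limitation is disclosed. The Discussion concedes bias from open conditions, and separately that the lack of randomisation may bias physiological results at higher doses. That stands: nothing is concealed, and open labelling is not in itself an error. What fails is the reason given for accepting it.

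A reader might go further on three points, and the documents do not support any of them.

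- *That placebo is the only comparator, so under-reporting on placebo yields a false excess on CBD.* Visit 2 is a full assessment before any product, and Visit 10 is a full assessment after CBD has stopped. The article defines no CBD-minus-placebo test of tolerability; such a test can only be inferred. The documents give no basis for any rate of under-reporting on placebo.
- *That the logbook suppresses placebo-period events.* The instructions for use are the same for placebo and CBD. Weekly calls encourage logbook completion, a rating scale is used from Visit 2, and investigators are to ask about events at every contact and record all of them. The Visit 1 sentence is loose wording.
- *That every recording is scored unmasked.* The article says investigators and researchers know the dose, but not who scores the stored files or whether they are coded. A condensed article commonly leaves that to the full protocol. Pain behaviour is also captured only where applicable, in healthy men.

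**Conclusion.** The point holds in a limited form. The PK argument in the Discussion is sound for PK and does not carry over to the primary hypothesis in the Background or to the purpose under Study design. For those, expectation or scoring bias aligned with the fixed dose order could create or mask a trend.

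Its size is unknown. The table in the working shows only that shifts of a few tenths of an SD would matter at the planned sample size. It depends on the assumed linear shift, the borrowed correlation of 0.5 and a trend analysis that the article does not specify. Laboratory values, plasma levels and instrument-recorded cardiovascular measures are much less exposed.

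Masked scoring is a cheap improvement rather than the correction of a stated error. The documents do not make a case for redesigning the placebo period.

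**What to change.** 1. Before offline scoring, give random visit codes to stored recordings that need reader judgement: TMS/EMG files for the silent period and SICI, seismocardiogram intervals, and any recorded pain behaviour. Existing staff score them without sight of visit or dose, and the codes are opened after scoring. If the full protocol already does this, one sentence saying so is enough. Cost: a little file handling and no extra reader.

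2. In the Discussion, confine the blinding defence to PK. State that tolerability and questionnaire results are open to expectation bias in either direction, and that conclusions on the primary hypothesis will be qualified accordingly. Cost: two sentences. Masked scoring does nothing for self-report, so this statement is needed even with item 1.

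3. As a minor point, replace the Visit 1 logbook wording ("record any side effects associated with the study product during the treatment phase") with the cause-neutral instruction already used at Visit 2 and in the Treatment Phase, so that it also agrees with the Adverse events section. Cost: one sentence.

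The escalation schedule, sample size and visit plan are unaffected.
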